### Biological management of caries, with best practice prevention

Dentinal caries is sealed into the tooth, and separated from the oral cavity by application of an adhesive restoration material over the decay, or by covering with a metal crown. Decay may, on occasion, be partially removed prior to the tooth being sealed. Injections are rarely needed. Retained roots, and teeth for which the crowns are unrestorable, or dental nerves (pulps) exposed with active caries (still progressing) or where the clinician decides the tooth is likely to cause the patient pain or infection before it exfoliates (falls out) are managed by extraction.

Best practice prevention is carried out in line with current guidelines and as described below.

### Best practice prevention alone

Dentists and other members of the dental team base patients’ treatment plans on best practice preventive care for teeth and oral health. This will involve four strands, all carried out according to current national guidelines [5,17,18]:

● Toothbrushing/self-applied topical fluoride use;

● Dietary investigation, analysis and intervention;

● Fissure sealants for secondary teeth; and,

● Fluoride varnish applied to primary and secondary teeth.

### Data collection, management and analysis

Outcome data is being collected through a clinician-completed Case Report Form (CRF) and via child and parent questionnaires. Table 1 details the scheduling of individual outcome data collection events, how each outcome is captured, by whom, and when.

**Table 1 T1:** FiCTION Trial: Schedule of outcome data collection events

**Event**	**Completed by:**	**Baseline examination appointment**	**Treatment appointments (Scheduled treatment or recall & unscheduled/ emergency)**	**Final appointment at 3 years post randomisation**
Bitewing Radiographs	GDP	Risk-based in line with guidance		
		**NOT A STUDY INVESTIGATION**		
Consent/Assent & Randomisaton	GDP	X		
ICDAS (CRF)	GDP	X		X
Adverse Event recording (CRF)	GDP		X	X
Pain: post treatment questions to GDP (CRF)	GDP		X	X
Cooperation (CRF)	GDP		X	X
Intervention Cost data (CRF)	GDP		X	X
Discomfort during treatment (DDQ8)	Parent		X	X
Quality of Life	Parent	X		X
Worry and Pain pre/post treatment questions to parent	Parent		X	X
Economic questions	Parent		X	X
MCDAS & worry	Child	X	X	X
Pain: pre/post treatment questions to child: VAS	Child		X	X

### Primary outcomes

#### *Pain (toothache)*

Assessments for pain from toothache are be made at each visit (treatment or recall) throughout the patient’s participation in the trial using the Dental Discomfort Questionnaire (DDQ8) completed by the parents [19]. In order to differentiate between pain originating from a decayed tooth and pain from other causes, the dentist forms a diagnosis based on patient/parent history and the clinical evidence available from examination, which is recorded on the CRF. This outcome is the number of children in each treatment arm experiencing toothache pain and the number of episodes of pain for each child in each arm during the 3-year follow-up period.

#### *Dental infection*

Assessments for infection are made at each visit (treatment or recall) throughout the patient’s participation in the trial. The outcomes are clinical (from examination by the child’s dentist) and radiographic signs (assessed by a dentist and an independent assessor). Clinical visual examinations for infection are specifically undertaken at every dental visit by the GDPs, and recorded on the CRF. These examinations are supplemented with independent examination of any bitewing radiographs that have been taken in line with Faculty of General Dental Practitioners guidelines [20] to record radiographic signs of inter-radicular pathology. The clinical detection criteria for the positive recording of infection are the presence of a swelling, dental abscess or draining sinus. Although GDPs are familiar with the signs and symptoms of infection we have developed the FiCTION training programme to specifically include the detection of infection and ensure it is reliably and reproducibly recorded.

Data for the primary outcomes of pain and infection are recorded during or following appointment times when the participant attends for both scheduled appointments and unscheduled/emergency appointments.

### Secondary outcomes

#### *Incidence of caries in primary and secondary teeth*

Detailed measurements of caries experience are recorded at baseline and final assessment by the GDPs using the CRF. The dentists measure both early and more advanced stages of dental caries. The stage or extent of caries is recorded using the International Caries Detection and Assessment System [21] which the participating dentists have received training in. The primary requirement for the examination is clean, dry teeth. All surfaces of all teeth are examined and the status of each recorded in terms of caries and restorations. Bitewing radiographs, taken in line with FGDP (UK) guidelines [20] (with blinded, independent assessment) are used as an independent measure of dental caries. However, as frequency of bitewing radiographs is based on caries risk assessment, and as some children may move out of the high risk group during the course of the trial, the frequency of bitewing radiographs taken for some children may reduce over the period of the study.

#### *Quality of Life*

Oral health related quality of life is measured at the beginning and end of the study. The measurement of quality of life in children is complicated by the rapid changes seen as children grow [22,23] including the development of children’s levels of literacy and understanding. For children under six years of age, the use of simple child-completed scales or questionnaires completed by parents as proxies is the usual solution [24].

Parents will be asked to complete a 16-item Parents’ Perception Questionnaire (PPQ) ([name] personal communication. OHRQoL Symposium, BSODR, Sheffield, 2011). The full length version of this measure has been found to be reliable and valid for use in the UK [25]. In addition, parents will be asked to provide a proxy evaluation of their child’s overall oral health-related quality of life by responding to two single item ratings worded:

“Would you say that the health of your teeth, lips, jaws and mouth is…?” with a 5-point response format ranging from ‘Excellent’ to ‘Poor’.

“How much does the condition of your teeth, lips, jaws or mouth affect your life overall?” with a response range from “Not at all” to “Very much”.

These questions are routinely used with the PPQ [26], and have been included in several UK studies [27].

Using a child-centred qualitative approach with participatory activities, children’s experiences and the acceptability of the three caries management strategies to children will be explored towards the end of trial [28].

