### Trial purpose and objectives

The primary objective is to compare the incidence of pain and infection experienced over a period of three years in 3–7 year-old children with caries in primary teeth when managed by one of these three treatment strategies.

The secondary objectives are to compare the three treatment strategies with respect to: incidence of caries in primary and secondary teeth, patient quality of life, cost-effectiveness over the period of the study, acceptability and associated experiences for patients and parents, and dentists’ preferences.

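### As quoted, the two global quality-of-life items ask parents about their own mouth and life, although they are meant as proxy ratings of the child

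*Protocol article*

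**What the plan says.** Quality of life is one of the listed secondary objectives ("patient quality of life", under Trial purpose and objectives). The Quality of Life section sets the timing: "Oral health related quality of life is measured at the beginning and end of the study".

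Two parent-completed instruments are described there. The first is the 16-item PPQ. The second is a pair of global ratings, introduced by saying that "parents will be asked to provide a proxy evaluation of their child’s overall oral health-related quality of life" and that they do so "by responding to two single item ratings worded". The two items then follow in quotation marks:

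- Item 1: "Would you say that the health of your teeth, lips, jaws and mouth is", answered on a five-point scale.
- Item 2: "How much does the condition of your teeth, lips, jaws or mouth affect your life overall", also answered on a graded scale.

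The support offered is prior use: "These questions are routinely used with the PPQ", together with inclusion in several UK studies. Table 1 lists the parent as the person completing Quality of Life, at the baseline examination and at the final three-year appointment.

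**The concern.** The sentence that introduces the items makes the child the subject of the rating. The items themselves make the respondent the subject, and the respondent is the parent. A parent who takes the words at face value reports on his or her own teeth and life.

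Treatment is randomised to the child. The article gives no reason to expect the parent's own oral health to differ between arms, since best practice prevention is part of all three strategies. Answers given about the parent therefore carry no information on the treatment comparison and dilute the answers given about the child. At stake is the sensitivity of two single-item ratings within one secondary outcome that is measured only twice.

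**Working it through.** No figure in the plan depends on this point, so there is nothing to reproduce. The check is textual, followed by a simple expression for the consequence.

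**Step 1: who answers.** The Quality of Life section says parents do. Table 1 agrees: its Quality of Life row names the parent alone, while measures completed by the child, such as the dental anxiety scale, have separate rows marked for the child. The items cannot be read as child self-report.

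**Step 2: whom the rating is meant to describe.** The introductory sentence calls it a proxy evaluation of the child.

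**Step 3: whom the wording describes.** Item 1 uses the second person once, for the mouth. Item 2 uses it twice, for the mouth and for life overall. Neither mentions the child, and the article gives no stem or instruction telling the parent to answer on the child's behalf.

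**Step 4: whether the wording is a paraphrase.** It is presented as the wording itself, in quotation marks.

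**Step 5: whether the stated justification settles it.** It does not. The article says the items routinely accompany the PPQ, but not whether the routine version is a self-report or a proxy form.

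Steps 2 and 3 disagree for both items.

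**Step 6: consequence.** Let C₁ and C₂ be the mean ratings in two arms if every parent rated the child. Let P be the mean if every parent rated himself or herself, taken as equal in the two arms. Let f be the share who rate themselves, also taken as equal in the two arms and unrelated to the child's rating. The expected arm means are (1 − f)C₁ + fP and (1 − f)C₂ + fP. Their difference is

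(1 − f)(C₁ − C₂).

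The documents do not give f, so these values are illustrative:

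- f = 0: 1 − 0 = 100% of the true difference remains.
- f = 25%: 1 − 0.25 = 75% remains.
- f = 50%: 1 − 0.50 = 50% remains.
- f = 100%: 1 − 1 = 0 remains.

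**Step 7: whether correction is still possible.** The first practice was ready to recruit on 21 September 2012, and full enrolment was projected for the end of June 2013. The final assessment is three years after randomisation, so none falls due before late September 2015. When the article was written, every final form and some baseline forms were still to be completed.

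**The case against.** The best counter-argument is that the questionnaire is not shown. The article condenses a fuller protocol. The issued form may carry a heading telling the parent to answer for the child, or may already use proxy wording, with the article having quoted a self-report version by mistake. Parents also complete the items at a child's dental visit and next to an instrument about their perceptions of the child, so many may answer about the child whatever the wording says. This stands. The mismatch is certain for the items as quoted, but not for what parents were given, and f could be well below 100%.

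A reader might infer that the two items measure the parent's oral health and so cannot detect any effect of the child's treatment. The documents do not support that. It follows only if the issued form carries this wording and every parent takes it literally. At any lower share the effect is attenuated, not lost.

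A reader might also infer that the quality-of-life outcome as a whole is biased towards no difference. That goes too far as well. The 16-item PPQ is listed first, the global items are additional to it, and this wording does not touch it.

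The objection does not remove the inconsistency. The article chose to state the wording, that wording conflicts with the sentence introducing it, and no other section corrects it. An analysis plan could not repair the wording of an item either.

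**Conclusion.** The point holds for the items as quoted: their stated purpose and their wording do not match. If the issued form is the same, the between-arm difference on these two items is attenuated to 1 − f of its true value. That rests on three assumptions: f is similar across arms, it is unrelated to the child's rating, and parents' own oral health does not differ by arm. The size cannot be fixed further because f is unknown.

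The scope is two supplementary single items of one secondary outcome. The PPQ, the primary outcome and the sample size are untouched. The point still deserves action, because checking and correcting are cheap and the protocol text needs correcting in either case.

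**What to change.** 1. Check the parent form that was actually issued.
2. If it already refers to the child, by wording or by instruction, correct the protocol text to show the version used. Nothing else is needed.
3. If it carries the quoted wording, replace *your* with *your child's* throughout both items (once in the first, twice in the second). Use the new page for all remaining baseline forms and all final forms, and correct the protocol text to match.
4. For these two items, do not use baseline values collected on the self-referring wording. A covariate for questionnaire version does not rescue them: it shifts a mean but cannot turn a parent's self-rating into a rating of the child.
5. Compare arms on the final-visit ratings. The mean difference at the end of follow-up is already among the quantities listed under Statistical methods, and randomisation supports that comparison without a baseline value.

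The cost is a minor amendment, one reissued questionnaire page, and the loss of some baseline values for these two items. With those values go any baseline adjustment or change analysis that would have relied on them.

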#### *Economic*

To allow a full understanding of cost-effectiveness and add value to the analysis, two different ways of measuring incremental costs will be compared; a time/material-based cost and the current cost to the NHS.

Time and material-based cost: an appropriate fee structure and an understanding of the opportunity costs will be essential prior to implementation of any arm of the trial. It is known that fee structures influence practice. However, they do not necessarily represent the costs related to the dentist’s time and materials and may result in perverse incentives. Furthermore, there is no specific fee for some of the procedures encompassed in the biological arm, despite different time and material costs. Consequently, a “procedure cost” based on time in the surgery and materials used will be applied for the common operative interventions in the Conventional with Prevention, Biological with Prevention and Prevention Alone arms. Data on resource use will be collected via the CRF for each enrolled patient for every scheduled and unscheduled visit, and include the number of dental visits, treatments undertaken and appointment duration. These data will be combined with a micro-costing study based on data recorded from direct observation of a number of centres during the trial. The micro-costing study will estimate the resources used to provide the interventions, e.g. equipment (disposable and reusable) consumables and staff mix. The costs of onward referral (for example, for hospital admission for extraction of painful teeth under general anaesthesia) will be obtained from existing data available within the NHS.

Current cost to the NHS: the payment systems in Scotland and England/Wales differ, therefore the costs of clinical interventions to the NHS will be calculated using the standard fees from the fee per item arrangements in Scotland and an agreed Unit of Dental Activity (UDA) value in England/Wales. The UDA information will be collected annually via a short survey sent to each participating practice. In the event that this information cannot be collected from practices, the PCT or equivalent body will be asked to provide this information. Fee per item information will be based on nationally available data (Information Services Division, Scotland). This costing strategy will allow actual NHS costs to be calculated whilst highlighting any variability in cost effectiveness resulting from the different payment systems.

Data on parental costs (time off work, child care costs and over-the-counter medications) will be collected using previously developed questionnaires. These questionnaires will be completed by the accompanying adult each time a child visits the dentist.

Cost-effectiveness analysis: the relative cost-effectiveness of each arm will be assessed by considering both the cost per infection-free patient and cost per pain-free patient. The incremental cost per pain/infection episode will be calculated, with usual dental care (conventional caries management) as the base case. Sensitivity analysis will be performed to test the robustness of the results to realistic variations in the levels of the underlying data.

#### *Acceptability of treatment strategies and experiences of patients and parents*

To measure the acceptability of the treatment strategies experienced, dental anxiety of children will be assessed. The Modified Child Dental Anxiety Scale - faces (MCDASf) is a rating scale based on faces instead of the original numeric form. The reliability and validity of MCDASf has previously been evaluated for use in children in the UK [29]. The MCDASf will be administered at baseline and every recall and treatment appointment to provide information on children’s perceptions of each dental experience throughout the study.

At the start of each appointment the child will be given a faces-based Visual Analogue Scale (VAS) to report on their level of anxiety prior to arriving at the dentist’s for their appointment. They will also be given a “faces” VAS following each treatment appointment to report on their level of anxiety during treatment.

Parents’ assessment of their child’s anxiety level prior to arrival at the dentist’s for their appointment and following treatment will also be recorded using a VAS.

Given the difficulty in measuring children’s attitudes towards treatment strategies, identified in the pilot rehearsal trial, the acceptability of the three treatment strategies will be explored using child-centred interviews which incorporate child participatory activities to allow children rather than adults to shape the data collection process [28].

Discomfort during dental treatment will be assessed using a VAS – completed by the child. A VAS is often used with children to assess self-reporting of such measures as fear or pain and can be used from a very young age with acceptable levels of reliability [24]. At the end of each appointment the child will be given a faces VAS to report on their levels of pain in relation to that particular visit. In addition, parents will also be asked to report on their perceptions of their child’s levels of pain regarding that particular visit to the dentist.

#### *Dentists’ preferences*

Exploration of dentists’ preferences between the 3 treatment strategies will be explored qualitatively through interviews/focus group using a method most convenient to study dentists, using topic guides derived from qualitative information collected during the FiCTION pilot rehearsal study.

### Data management and statistical methods

#### *Data management*

To preserve confidentiality, all patients will be allocated a unique study identifier, which will be used on all data collection forms and questionnaires; names or addresses will not appear on completed questionnaires or case report forms. Only a limited number of members of the research team will be able to link this identifier to patient-identifiable details (name & address) which will be held on a password- protected database. The Chief Investigators will preserve the confidentiality of participants in the study and the Sponsor organisation (University of Dundee) will ensure that the study complies with the Data Protection Act 1998 and that all investigators and staff involved with the study comply with its requirements with regard to the collection, storage, processing and disclosure of personal information uphold the Act’s core principles. Published results will not contain any personal data that could allow identification of individual participants.

#### *Statistical methods*

The primary outcome, the proportion of children reporting either pain or sepsis during the three year follow up period, will be analysed using a mixed model with a binomial error structure. The dependent variables will be a binary indicator of pain or sepsis; variation between strata (dental practices) will be fitted as a random effect; differences between study treatments will be fitted as fixed effects. Estimates of the relative risk of pain or sepsis in the three groups will be presented in the form of odds ratios and associated 95% confidence intervals. As secondary analysis of the primary outcome, pain and sepsis will be analysed separately using the same approach.

Secondary outcomes will be analysed using multilevel modelling (repeated measures nested within children nested within general dental practices) with an appropriate error structure (binomial for binary variables, normal for continuous variables). Variation between dental practices, variation between children and variation between occasions will be modelled as random effects; difference between groups will be included as fixed effects. Within this framework we will be able to estimate:

1. The mean difference between groups at the end of the follow up period;

2. The mean difference between groups across the whole of the follow up period; and

3. The difference in the rate of change of the outcome across the follow up period

For each outcome the primary comparison of interest will be specified in the statistical analysis plan which will be finalised prior to completion of data collection.

Economic analysis will use estimates of costs and effects estimated for each trial participant to calculate the incremental cost-effectiveness ratios for the follow-up period. Where appropriate the analysis will mirror the statistical analysis. The perspective of the analysis will be the patient and the care provider. The results of the analyses will be presented as point estimates of mean incremental costs and effects. Sensitivity analysis will be used to assess the robustness of the results to realistic variations in the levels of the underlying data. In addition, techniques such as bootstrapping will be used alongside sensitivity analysis to address uncertainty. Data will be presented as cost-effectiveness acceptability curves.

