### Practices

#### *Target sample size*

The primary outcome will be the proportion of children reporting either pain or infection during the three years of follow up. Based on evidence from previous studies on similar populations with no restorations [1,6] and conventional restorations and the Hall Technique [11], infection rates of 20%, 10% and 3% respectively are expected. Using the “sampsi” procedure (a sample size calculation based on a two-sample test of proportions assuming a normal approximation and incorporating a continuity correction) in Stata version 9 [16], and assuming a significance level of 2.5% (to allow for multiple testing involved in a three arm trial) the following are needed:

● two groups of 334 children to detect a difference in rates between 10% and 20% with 90% power

● two groups of 334 children to detect a difference in rates between 3% and 10% with 90% power

The sample size has been increased by an arbitrary inflation factor of 1.09 (giving 365 children per arm at end of follow up) to allow for adjustment of estimates of effect size taking into account variation between randomisation strata (dental practices). Allowing for a loss to follow up over three years of 25% (based on experience other clinical trials in Primary Care, including the FiCTION Pilot Trial), we will need to randomise 487 children to each arm of the trial.

We are aiming to recruit 50 practices with a total of 80–100 dentists. Based on the findings from the Pilot Rehearsal Trial, from these fifty practices 18,717 children will be invited to attend for screening with an expected 12,166 (65%) of these children actually attending and agreeing to be screened for the study. It is expected that 1825 children (15% of those screened) will be eligible for the Trial. Of these, it is anticipated that 1460 (80% of those eligible) will consent to be randomised, with 487 children allocated to each of the three study arms. Figure 1 shows projected numbers of participants in the trial in a Consort flow diagram.

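### The 2.5% significance level that sizes the trial is not carried into the primary analysis, which presents 95% confidence intervals

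*Protocol article*

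**What the plan says.** In Target sample size, the protocol article expects different event rates in the three strategies: "infection rates of 20%, 10% and 3% respectively are expected", for no restorations, conventional restorations and the Hall Technique. It sizes the trial "assuming a significance level of 2.5% (to allow for multiple testing involved in a three arm trial"), and applies that level to two comparisons:

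- "two groups of 334 children to detect a difference in rates between 10% and 20% with 90% power", which is prevention alone v conventional;
- "two groups of 334 children to detect a difference in rates between 3% and 10% with 90% power", which is conventional v biological.

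In Statistical methods, the primary outcome (pain or sepsis over three years) is analysed with a binomial mixed model, with treatment as a fixed effect and practice as a random effect. The treatment estimates "will be presented in the form of odds ratios and associated 95% confidence intervals". That section does not repeat the 2.5% level and gives no multiplicity adjustment, global test or testing order. It leaves the choice of the primary comparison for each outcome to the SAP. The level of the interval is not part of what it leaves to the SAP.

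**The concern.** The article gives two levels for the same comparisons. The design allows 2.5% for each of two contrasts, which is the Bonferroni split of 5%. The analysis presents intervals that correspond to 5% for each contrast. As the interval is the only inferential output fixed for the primary outcome, many readers will judge a contrast by whether its interval excludes an odds ratio of 1. Used in that way, the interval doubles the per-contrast error rate that the design assumed.

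The two levels can also give different answers. A contrast with a p-value between 0.025 and 0.05 would have a 95% interval that excludes 1 and yet would fail a 2.5% test. The article gives no rule for which governs. The trial is meant to inform service policy and teaching, so this should be settled before the data are seen.

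**Working it through.** **Inputs** (Target sample size): rates of 20%, 10% and 3%; significance 2.5%; power 90%; "a sample size calculation based on a two-sample test of proportions assuming a normal approximation and incorporating a continuity correction". The article does not state the sidedness, so it is checked below.

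**1. Reproduce the stated 334.** With p̄ the mean of the two rates and d their difference:

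- n₀ = [z(1−α/2)·√(2p̄(1−p̄)) + z(0.90)·√(p₁(1−p₁)+p₂(1−p₂))]² / d²
- n = (n₀/4)·[1 + √(1 + 4/(n₀d))]² (continuity correction)

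At two-sided α = 0.025, z(0.9875) = 2.2414 and z(0.90) = 1.2816.

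- 10% v 20%: n₀ = (2.2414×0.50498 + 1.2816×0.50000)²/0.10² = 314.2. After correction n = 333.9, so **334**.
- 3% v 10%: n₀ = (2.2414×0.34864 + 1.2816×0.34511)²/0.07² = 305.6. After correction n = 333.6, so **334**.

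Both match the article. The other readings tried do not:

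| Setting | 10% v 20% | 3% v 10% |
|---|---|---|
| Two-sided 2.5%, corrected | 334 | 334 |
| Two-sided 2.5%, uncorrected | 315 | 306 |
| One-sided 2.5%, corrected | 286 | 287 |
| Two-sided 5%, corrected | 286 | 287 |

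**2. What the 2.5% level costs in children.** The article's chain is 334 × 1.09 = 364.06 (stated as 365), 365/0.75 = 486.7, so 487 per arm, and 3 × 487 = 1461. The same chain from 287 is 287 × 1.09 = 312.8, so 313; 313/0.75 = 417.3, so 418; and 3 × 418 = 1254. The difference is 1461 − 1254 = 207 children, or 207/1461 = 14% of the sample. They are there to pay for the stricter level.

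**3. Family-wise error for the two sized contrasts.** Assume the global null, equal arms and no gating test. The two contrasts share the conventional arm, so their test statistics have a correlation of 0.5 in absolute value. Four million simulated sets of three arm means give:

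| Level per contrast | Bonferroni bound | If independent | With shared arm |
|---|---|---|---|
| 5% (95% interval) | 10% | 9.75% | 9.1% |
| 2.5% (97.5% interval) | 5% | 4.94% | 4.6% |

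**4. Cost of matching the interval to the design.** The ratio of critical values is 2.2414/1.9600 = 1.144, so a 97.5% interval is about 14% wider on the log-odds scale. As a guide on the risk-difference scale, take 20% v 10% with 365 per arm and ignore practice effects. The standard error is √(0.20×0.80/365 + 0.10×0.90/365) = 0.0262. The half-width is 1.960 × 0.0262 = 5.1 percentage points at 95% and 2.241 × 0.0262 = 5.9 points at 97.5%.

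**The case against.** The strongest reply is that the 95% level is a statement about presentation. The article nowhere sets a 5% test or makes an interval that excludes 1 the criterion for success. The only significance level it states is 2.5%, and nothing withdraws it. The SAP, which is not shown, could test at 2.5% and show 95% intervals as description. This stands, and it limits the point. A reader might infer that multiplicity control is lost at analysis, but the document does not show that. The 9.1% figure holds only if the 95% intervals are used as the test. The reply does not remove the mismatch, because the article fixes the interval level itself and does not say how it relates to the 2.5%.

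Secondly, a 95% interval does not by itself imply loss of control. With exactly three arms, a global test at 5% followed by pairwise tests at 5% controls family-wise error. This is correct, and it makes 97.5% intervals one remedy among others. The article states no such gate, however, so it is no defence of the present text.

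Thirdly, a reader might add that 2.5% per test is too lenient because three arms give three pairwise contrasts. The document does not support this. It sizes two contrasts, for which 2.5% is exactly the Bonferroni level, and never calls biological v prevention alone confirmatory. The naming of primary comparisons may fairly be left to the SAP.

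**Conclusion.** The point holds in limited form: the text is wrong as written and should be fixed. The design level of 2.5% drives the 334 per group, and the analysis section presents intervals at a level that does not correspond to it. If those intervals are taken as the inference, family-wise error for the two sized contrasts is about 9.1% where the design implies about 4.6%. This rests on the global null, equal arms, a shared conventional arm, no gating test and the interval serving as the decision rule. The point is short of critical: the article declares no 5% test, an SAP could still apply 2.5%, and the data collected, model, point estimates and sample size are all unaffected.

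**What to change.** State in the analysis section, or in the SAP before it is finalised, that the two sized contrasts (prevention alone v conventional, biological v conventional) are each tested at two-sided 2.5%, and report 97.5% confidence intervals for their odds ratios. If 95% intervals are also shown, say that they are descriptive and that the 2.5% level governs. Treat biological v prevention alone as supportive unless the SAP makes it confirmatory, in which case the SAP should say how error is controlled across all three contrasts.

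The cost is a sentence or two of text and intervals about 14% wider, taken from the same fitted model. No more children are needed, because 334, 365 and 487 per arm already allow for the 2.5% level.
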